## Abstract

**Introduction:**

Emergency caesarean section (ECS) qualifies as a psychological trauma, which may result in postnatal post-traumatic stress disorder (PTSD). Maternal PTSD may not only have a significant negative impact on mother–infant interactions, but also on long-term infant development. The partner’s mental health may also affect infant development. Evidence-based early interventions to prevent the development of postpartum PTSD in mothers are lacking. Immediately after a traumatic event, memory formation is vulnerable to interference. There is accumulating evidence that a brief behavioural intervention including a visuospatial task may result in a reduction in intrusive memories of the trauma.

**Methods and analysis:**

This study protocol describes a double-blind multicentre randomised controlled phase III trial testing an early brief maternal intervention including the computer game ‘Tetris’ on intrusive memories of the ECS trauma (≤1 week) and PTSD symptoms (6 weeks, primary outcome) of 144 women following an ECS. The intervention group will carry out a brief behavioural procedure including playing Tetris. The attention-placebo control group will complete a brief written activity log. Both simple cognitive tasks will be completed within the first 6 hours following traumatic childbirth. The intervention is delivered by midwives/nurses in the maternity unit.

The primary outcome will be differences in the presence and severity of maternal PTSD symptoms between the intervention and the attention-placebo control group at 6 weeks post partum. Secondary outcomes will be physiological stress and psychological vulnerability, mother–infant interaction and infant developmental outcomes. Other outcomes will be psychological vulnerability and physiological regulation of the partner and their bonding with the infant, as well as the number of intrusive memories of the event.

**Ethics and dissemination:**

Ethical approval was granted by the Human Research Ethics Committee of the Canton de Vaud (study number 2017–02142). Dissemination of results will occur via national and international conferences, in peer-reviewed journals, public conferences and social media.

**Trial registration number:**

NCT 03576586.

Strengths and limitations of this studyThis multicentre randomised controlled trial will test the effects of an early brief behavioural intervention carried out by midwives/nurses on the labour ward.The primary outcome will be the presence and severity of maternal post-traumatic stress disorder symptoms at 6 weeks.The early brief intervention, conducted in the same hospital where the traumatic event occurred, includes a visuospatial task aimed at competing with sensory aspects of the traumatic memory before it has been fully consolidated.Methodological rigour, including a double-blind design, an active control group, concealment of random allocation, regular monitoring and prospective trial registration, limits risk of bias.Some outcomes are measured with self-report questionnaires, which may induce a social desirability bias.

## Introduction

### Childbirth and post-traumatic stress disorder

Though childbirth is a common and often fulfilling event, one-third of mothers rate their childbirth as traumatic.^1^ Childbirth can meet diagnostic criteria for a traumatic event, if women perceived their life and/or the life of their baby to be in danger.^2^ Post-traumatic stress disorder (PTSD) related to childbirth is diagnosable in around 3%–4% of women.^3 4^ According to the Diagnostic and Statistical Manual of Mental Disorders, Fifth Edition (DSM-5), PTSD consists of four symptom clusters (intrusions, avoidance, hyperarousal and negative cognitions and mood) and can be diagnosed at least 1 month after the traumatic stressor occurred.^2^ Comparing different modes of childbirth, obstetric complications, such as emergency caesarean section (ECS), produce higher rates of postnatal PTSD (19%–39%).^3^ ECS is a relatively frequent event, and there is thus a need to better identify and support women who are vulnerable to developing PTSD following an ECS.

Postnatal PTSD can significantly influence the experience of subsequent pregnancies, with increased risk of maternal stress and its associated risks of intrauterine growth retardation, premature birth and low birth weight.^5–7^ It can lead to a fear of subsequent pregnancy and childbirth, sexual problems and avoidance of medical care.^8 9^ Postnatal PTSD can also have important negative consequences for breastfeeding, the attachment relationship with the baby and mother–infant interactions, with a subsequent detrimental impact on the development of the child, as well as for the couple relationship.^7 10–13^ PTSD is also highly comorbid with depression, for which there is substantial evidence of long-term negative effects on child development and behaviour.^14–16^ Estimated economic costs of perinatal mental health problems are about £8.1 billion for each 1 year cohort of UK births, of which 72% relate to adverse impacts on the child rather than the mother.^17^ In Switzerland, 16.7% of women in the perinatal period used mental health services.^18^ New and innovative evidence-based interventions are, therefore, needed to reduce those costs by preventing the development of postnatal PTSD.^19^

To date, research investigating PTSD symptoms in partners following ECS is missing. Most studies on partners so far have focused on postnatal depression reporting that 1%–8% experience depression symptoms in the first 6 weeks and 5%–6% at 3–6 months following childbirth without complications,^20–22^ with increased risk following high-risk situations.^23^ In one study, 5% of partners reported severe intrusions and avoidance symptoms at 9 weeks post partum.^24^ Although the influence of partner mental health is understudied, it also seems to negatively impact child outcomes.^25–27^ Thus, partner mental health needs to be better understood in order to help the partner and to support family and child outcomes.

### Physiological stress responses associated with PTSD

Traumatic exposure activates the hypothalamic–pituitary–adrenal (HPA) axis, a cascade-like hormonal system resulting in the release of cortisol from adrenal cortex cells in body fluids. In parallel, the organism activates the more rapidly mobilising autonomic nervous system (ANS) resulting in the release of norepinephrine from nerve terminals of the sympathetic nervous system as well as epinephrine and norepinephrine from the adrenal medulla.^28^ While the HPA axis shows the above stress-related reactivity, it also shows a basal activity with circadian variations in the respective hormones. For instance, cortisol peaks 30–45 min after awakening (the so-called cortisol awakening response (CAR)) and gradually declines throughout the day with lowest levels early during the sleep.^29 30^

Specific patterns of HPA axis functioning have been shown in PTSD^31^ although this has so far not been studied after traumatic childbirth. While studies indicate that individuals with PTSD show different patterns of HPA axis functioning to those without PTSD, there is little consistency in the specificity of these patterns.^32–38^ A meta-analysis examining diurnal cortisol levels in adults with PTSD showed that low cortisol levels were not related to PTSD in general, but rather to trauma exposure and comorbidities.^39^ Finally, a recent study in a postnatal population found a negative association between symptoms of re-experiencing and diurnal cortisol slopes in mothers of preterm children.^40^ Concerning cortisol reactivity to a subsequent stressor, again, results are discrepant.^41 42^

Although HPA axis reactivity following stress or trauma is thought to be adaptive, acute or chronic exposure to stress has been shown to have deleterious effects.^43 44^ It may not only result in dysfunctions of HPA reactivity, but also in health-relevant changes in the basal activation of this system.^45^ Overall, these studies show the strong implication of the HPA axis dysregulation in the development and maintenance of PTSD, although studies in postnatal populations are scarce.

Reduced heart rate variability (HRV), an indicator of autonomic flexibility, has been found to be related to psychopathological processes.^46^ Individuals with PTSD show lower levels of HRV in comparison with trauma-exposed individuals without PTSD or healthy controls.^47 48^ However, the relationship of PTSD and HRV has so far not been studied in a postnatal population.

Sleep in PTSD is also disrupted. Sleep disturbance (ie, difficulty falling or staying asleep) and recurrent distressing dreams are both diagnostic criteria for PTSD,^2^ with 70%–91% of patients with PTSD suffering from subjective sleep disturbances and 19%–71% reporting nightmares.^49^ Findings from experimental research indicate that sleep on the first night after trauma may be important for the development of subsequent intrusive memories of the index trauma. One study found that totally sleep deprived participants reported fewer intrusive memories after a laboratory stressor compared with those who slept,^50^ though findings are mixed.^51–53^ Thus, it is important to assess sleep over time following a real-world traumatic event, such as following an ECS. To date, no studies to our knowledge have examined sleep in postpartum PTSD.

### Maternal PTSD and infant physiological stress responses

Maternal PTSD and its associated dysfunction of the HPA axis can also impact on the stress regulation of the offspring,^54–63^ such as the infant’s HPA secretion patterns.^64–66^ A growing body of neuroendocrine research supports the notion that an altered maternal HPA axis functioning plays a role in the intergenerational transmission of stress-related psychopathology from parents.^67 68^ Overall, findings suggest that PTSD symptoms and cortisol levels in mothers are important to assess, prevent and/or treat as they may affect the relationship with the infant^69–72^ and impact the child’s later regulative abilities.^54^ Some authors have suggested low maternal cortisol as a possible mechanism contributing to the mother’s difficulty in sensitively attuning to her infant’s cues, which in turn impacts on the infant’s reactivity to and recovery from a stressor.^73–78^

In contrast, studies assessing the role of ANS in the intergenerational transmission of stress in the postpartum period are so far scarce. Lifetime maternal psychopathology and maternal postnatal psychopathology have been found to be related with reduced HRV of their infants.^79^ Furthermore, mothers with anxiety symptoms during the pregnancy and their infants showed lower HRV^80^ and there was a higher sympathetic activation in children of mothers with abuse histories.^81^ However, to our knowledge, none of the previous research has investigated the autonomic functioning in offspring of mothers with PTSD.

### Developing an early intervention inspired by behavioural and cognitive neuroscience

To date, there is a lack of evidence-based early interventions for women following a traumatic childbirth.^82^ At the heart of PTSD are intrusive memories of the traumatic event, in which the person re-experiences aspects of the traumatic event, inflicting significant distress.^2^ They have also been indicated as a precursor to the disorder.^83^ Intrusive memories of trauma comprise sensory-perceptual images that are proposed to occur due to excessive perceptual (sensory) processing during a trauma.^84^

The way in which individuals process a traumatic event influences their later intrusive memories of the trauma. Evidence from laboratory-based experiments have demonstrated that a brief behavioural intervention, including a reminder cue, mental rotation and a visuospatial task (Tetris), can significantly reduce the frequency of intrusive images following exposure to traumatic film material.^85 86^ One study showed that individuals who were instructed to engage in conceptually driven processing, relative to those engaged in sensory-based, data-driven processing, reported more intrusive memories to a traumatic film.^87^ It has been hypothesised that tasks which interfere with data-driven processing, such as sensory-perceptual, visuospatial tasks, may reduce the occurrence of intrusive memories of an index event.^85 86^ Visuospatial cognitive tasks, such as the computer game Tetris, are thought to compete for resources with visuospatial images.^88^ Studies of memory consolidation have shown that human memories are likely to still be malleable within 10 min to 6 hours, at which point the memory is thought to stabilise consolidation, making it more resistant to interference from a competing memory.^89–91^ This indicates that such a working memory task may be most beneficial if delivered within approximately the first 6 hours following a traumatic event (see ref. 92 for a review).

Two recent translational studies presented preliminary evidence for the efficacy of a brief intervention (including Tetris) in reducing the number of traumatic intrusive memories (over 1-week post-trauma) in patients arriving at an accident and emergency department (vs attention placebo)^93^ or in women in the first hours following ECS, the latter when compared with a treatment-as-usual control group.^4^ In the latter study, per-protocol analyses also showed significantly lower re-experiencing symptoms at 1 week and lower rates of PTSD diagnosis at 1 month following ECS (secondary outcomes).^4^

### Aims of the present study

The objectives of the present study are to investigate the effects of an early brief, behavioural intervention procedure (including the computer game Tetris) delivered in the hospital context within 6 hours of the trauma, on maternal mental health and infant development after a traumatic childbirth (ECS). The primary outcome measure will be the presence and the severity of maternal PTSD symptoms at 6 weeks. Secondary objectives will be to measure the impact of this intervention on intrusive memories of the trauma, on stress exposure and perception, on other indicators of maternal psychological vulnerability (including acute stress disorder (ASD), PTSD, anxiety, depression and sleep), on physiological stress reactivity, on physiological regulation, on mother–infant interactions and on infant development. The Swiss TrAumatic biRth Trial (START) study also aims to investigate additional maternal and partner psychological vulnerability, partner physiological regulation, partner–infant bonding and measures related to the acceptability and expectancy of the intervention.

## Methods

### Study design

We will conduct a multicentre double-blind randomised controlled trial (RCT) with minimal risk testing the effect of an early brief behavioural intervention including computer game play for women at risk of PTSD in the hospital soon following an ECS and their infant, compared with an attention-placebo control task.

### Study population, recruitment, group allocation and blinding

All women, who have an ECS ≥34 weeks gestation, give birth to a live baby, and give written consent are eligible to participate. In addition, they have to answer with a score of ≥2 separately for at least two out of four screening questions regarding perceived threat.^94^ All screening questions are answered on a 7-point Likert scale (1=not at all, 7=extremely): Did you think that your life was in danger? Did you think that your baby’s life was in danger? Did you feel frightened during the birth? Did you feel helpless during the birth?

Exclusion criteria include: established intellectual disability or psychotic illness, insufficient French-speaking level to participate in assessments, severe illness of mother or infant (eg, cancer, cardiovascular disease, severe neurodevelopmental difficulties and malformations) or if the infant requires intensive care, and alcohol abuse and/or illegal drug use during the pregnancy.

Following an ECS and once the mother has sufficiently recovered, the mother’s midwife/nurse will assess eligibility and if eligible, will inform the mother about the study. After providing written and informed consent to be screened, participants will be screened immediately for perceived threat of the mother and/or child with four screening questions. If participants score ≥2 separately for at least two out of the four questions, they will be randomly assigned to either the intervention or attention-placebo control group. We aim to recruit 144 women and their infants (see the Sample size calculation section).

If the woman agrees, then the partner will also be informed about the study. Inclusion criteria for the partners are that they were present at the childbirth and give written consent. Partners are excluded if they do not speak French sufficiently well to participate in assessments. All participants will be reimbursed for their time and effort.

The allocation ratio of randomisation is 1:1. The randomisation sequence will be generated using a computer-generated block randomisation (StataCorp 2017. Stata Statistical Software: Release 15) using blocks of sizes 2, 4 and 6 over 144 participants per stratum (stratified by research centre). Opaque envelopes will be prepared in advance, numbered sequentially by alternating between stratums by block. After conducting the baseline assessment, the clinical midwife/nurse will open the envelope and announce the cognitive task to be carried out (ie, the cognitive visuospatial task or the attention-placebo control task) to the participant.^95^ All members of the research group as well as participants are blind to group allocation. All participant data will be coded to ensure confidentiality. After completing the 15 min cognitive tasks, both women of the control and intervention group will complete the same assessments, as shown in table 1; see figure 1 for an overview of the study variables.

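### The perceived-threat screen can be passed on faint fright and helplessness alone, and the graded scores it yields are not fixed as a covariate in 6-week models whose stated baseline adjustment cannot be made

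*Protocol article*

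**What the plan says.** All statements are in the protocol article.

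- **What makes a birth traumatic** (Introduction, Childbirth and post-traumatic stress disorder): "Childbirth can meet diagnostic criteria for a traumatic event, if women perceived their life and/or the life of their baby to be in danger".
- **Purpose of the screen** (Methods, Study population, recruitment, group allocation and blinding): women are "screened immediately for perceived threat of the mother and/or child with four screening questions".
- **Scale**: "All screening questions are answered on a 7-point Likert scale (1=not at all, 7=extremely".
- **Items**: two ask about danger to life, "Did you think that your life was in danger? Did you think that your baby’s life was in danger"; two do not, "Did you feel frightened during the birth? Did you feel helpless during the birth".
- **Rule**: "they have to answer with a score of ≥2 separately for at least two out of four screening questions regarding perceived threat". Neither danger item is required.
- **Population** (Study design): "women at risk of PTSD in the hospital soon following an ECS".
- **Order of events** (same section as the screen): screening comes before random assignment, and the envelope is opened after the baseline assessment.
- **Primary models** (Data management and statistical analyses): linear regression of the 6-week PCL-5 and CAPS-5 subscale and total scores, adjusted for centre and for each outcome's baseline value. Further covariates are added if univariate tests find them significant. PTSD diagnosis is compared by logistic regression, with covariates found in the same way.
- **Schedule** (Table 1, mother): CAPS-5 and PCL-5 appear only at 6 weeks and 6 months.

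**The concern.** A screen described as one of perceived threat to mother or child should admit women who perceived such a threat. This one can be satisfied by the two items that do not ask about it, at the lowest score above none. If women with little perceived threat have fewer symptoms at 6 weeks, or less for the intervention to prevent, they take places in a fixed target of 144 and reduce power.

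The analysis section then leaves out a variable suited to the problem. Perceived threat is a plausible predictor of 6-week symptoms and is known for every woman before allocation. The stated adjustment relies instead on baseline values that the two primary instruments do not have, and on a data-driven choice of the remaining covariates.

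**Working it through.** **1. What the rule admits.** Write the answers in the order own life, baby's life, frightened, helpless, each from 1 to 7.

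- Possible patterns: 7^4 = 2401.
- Failing patterns: all four items at 1 (1 pattern), or exactly one item at 2 or more (4 × 6 = 24). Total 25.
- Passing patterns: 2401 − 25 = 2376.
- Passing with both danger items at 1: the other two must both be 2 or more, so 6 × 6 = 36. They run from 1, 1, 2, 2 to 1, 1, 7, 7.
- Failing although one danger item is 2 or more: that item takes 2 to 7 and the rest are 1, so 2 × 6 = 12. The pattern 1, 7, 1, 1 is one of them.

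So the rule departs from the Introduction's condition in both directions. These are counts of answer patterns. They are not proportions of women, and no share of women follows from them.

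**2. Possible loss of power.** The document gives no share f of randomised women with both danger items at 1. The following is an assumption with a range, and its zero effect in those women is the extreme case. With equal SDs, the standardised effect becomes d × (1 − f) and the required n is multiplied by 1/(1 − f)^2.

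The plan's own figure comes first: 120 women for d = 0.30, 80% power, α = 0.05. The two-sided formula gives 2 × (1.960 + 0.842)^2 / 0.30^2 ≈ 174.4, so 175 per arm and 350 in total; 60 per arm gives 37.6% power. The 120 does not reproduce. That is a separate matter, so two starting points are shown: d = 0.30 as stated, and d = 0.51, the effect for which 60 per arm does give 80% (2.802 × √(2/60) = 0.511).

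| Assumed f | Factor on n | Power, 60 per arm, d = 0.30 | Power, 60 per arm, d = 0.51 |
|---|---|---|---|
| 0% | 1.00 | 37.6% | 80.0% |
| 10% | 1.23 | 31.5% | 71.3% |
| 20% | 1.56 | 25.9% | 61.1% |
| 30% | 2.04 | 20.9% | 50.0% |

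Nothing in the document says which row applies, or that f is as high as 10%. A partial effect in these women would make every loss smaller.

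**3. Bias.** Screening precedes random assignment, so women with low threat scores fall in either arm by chance. The effect is on power and on the population described, not on the validity of the comparison.

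**4. The stated adjustment.** Set the analysis section beside Table 1. The models call for the baseline value of each outcome, but for CAPS-5 and PCL-5 the first measurement is the 6-week outcome itself. That term cannot be fitted for the primary outcomes. What remains is centre and whatever passes a univariate test.

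**5. What the threat score could add.** A covariate correlated r with the outcome removes a share r^2 of the residual variance. For an assumed r of 0.3 to 0.5 that is 0.3^2 = 9% to 0.5^2 = 25%. The document gives no value of r.

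**The case against.** A reader might infer more: that women who perceived no danger to life cannot, by the protocol's own definition, develop birth-related PTSD, and so are certain to dilute the primary comparison. The document does not support this. The Introduction says that perceived danger is enough for childbirth to meet the criteria, not that it is the only way. The Abstract calls emergency caesarean section a psychological trauma without any condition on perception, and the Aims equate it with traumatic childbirth. The primary models use continuous symptom scores, on which any woman can score. Diagnosis, where the trauma criterion would matter most, is a separate comparison described after the secondary aims.

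Two figures could also mislead. That 2376 of 2401 patterns pass (99.0%) says nothing about women; on the same count only 36 of 2376 have both danger items at 1. And the 19%–39% PTSD rate in the Introduction is given for obstetric complications such as emergency caesarean section, so it cannot serve as the rate among women who perceived danger and then be diluted again.

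The four items come from a cited instrument, whose scoring cannot be checked here, and broad entry is a legitimate choice. Requiring a danger item would still exclude 1, 7, 1, 1, and would turn away 1, 1, 7, 7 while admitting 2, 1, 2, 1. These objections stand.

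It can further be said that covariates belong in the analysis plan, which is not shown. That is so where a protocol is silent. Here it is not: it states a baseline adjustment that cannot be made and a significance-based selection rule. That part of the point survives.

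**Conclusion.** The point holds in limited form. The screen can be passed on fright and helplessness at 2 of 7 with no perceived danger to either life, so it does not ensure the condition it is described as testing. This may lower symptom levels and power. The size cannot be derived, since the share of such women and the effect in them are both unknown; the table above is a set of scenarios. There is no bias between arms and no case for calling these women incapable of PTSD.

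The firmer part needs no assumption. The primary models, as written, depend on baseline values that CAPS-5 and PCL-5 do not have and on covariates chosen by univariate significance, while a graded pre-allocation measure of perceived threat is given no fixed place in them. Using it is an inexpensive improvement; its gain in precision depends on a correlation the document does not report.

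**What to change.** 1. In the 6-week CAPS-5, PCL-5 and PTSD-diagnosis models, enter the pre-allocation perceived-threat score as a fixed covariate whatever its univariate p-value. State one definition before the data are seen, for example the higher of the two danger-to-life items. Remove or correct the reference to baseline values for outcomes that have none.
2. Add a supportive analysis in women scoring at least 2 on at least one danger-to-life item. Membership is settled before allocation, so the comparison remains randomised. It is smaller and should be labelled supportive.
3. Reconcile the wording of the Introduction and the eligibility section: either say that fright and helplessness count as perceived threat for entry, or describe the screen as broader than danger to life. The eligibility rule itself need not change.

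Cost: one model term, one extra analysis and a sentence or two. There is no recruitment cost and no new question to ask. The four item scores must be kept for each mother, not only the pass or fail; Table 1 lists these questions for partners but not for mothers. In the logistic model the odds ratio becomes conditional on the threat score and should be reported as such.
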